## Abstract

**Introduction:**

Ear pain is the most prominent symptom of childhood acute otitis media (AOM). To control the pain and reduce reliance on antibiotics, evidence of effectiveness for alternative interventions is urgently needed. This trial aims to investigate whether analgesic ear drops added to usual care provide superior ear pain relief over usual care alone in children presenting to primary care with AOM.

**Methods and analysis:**

This is a pragmatic, two-arm, individually randomised, open, superiority trial with cost-effectiveness analysis and nested mixed-methods process evaluation in general practices in the Netherlands. We aim to recruit 300 children aged 1–6 years with a general practitioner (GP) diagnosis of AOM and ear pain. Children will be randomly allocated (ratio 1:1) to either (1) lidocaine hydrochloride 5 mg/g ear drops (Otalgan) one to two drops up to six times daily for a maximum of 7 days in addition to usual care (oral analgesics, with/without antibiotics); or (2) usual care. Parents will complete a symptom diary for 4 weeks as well as generic and disease-specific quality of life questionnaires at baseline and 4 weeks. The primary outcome is the parent-reported ear pain score (0–10) over the first 3 days. Secondary outcomes include proportion of children consuming antibiotics, oral analgesic use and overall symptom burden in the first 7 days; number of days with ear pain, number of GP reconsultations and subsequent antibiotic prescribing, adverse events, complications of AOM and cost-effectiveness during 4-week follow-up; generic and disease-specific quality of life at 4 weeks; parents’ and GPs’ views and experiences with treatment acceptability, usability and satisfaction.

**Ethics and dissemination:**

The Medical Research Ethics Committee Utrecht, the Netherlands, has approved the protocol (21-447/G-D). All parents/guardians of participants will provide written informed consent. Study results will be submitted for publication in peer-reviewed medical journals and presented at relevant (inter)national scientific meetings.

**Trial registration:**

The Netherlands Trial Register: NL9500; date of registration: 28 May 2021. At the time of publication of the study protocol paper, we were unable to make any amendments to the trial registration record in the Netherlands Trial Register. The addition of a data sharing plan was required to adhere to the International Committee of Medical Journal Editors guidelines. The trial was therefore reregistered in ClinicalTrials.gov (NCT05651633; date of registration: 15 December 2022). This second registration is for modification purposes only and the Netherlands Trial Register record (NL9500) should be regarded as the primary trial registration.

STRENGTHS AND LIMITATIONS OF THIS STUDYThe pragmatic, open design enhances the applicability of the trial findings in daily practice.The pragmatic, open design is most suited to address the key secondary outcomes of the impact of the analgesic ear drops on the proportion of children consuming antibiotics and its cost-effectiveness in everyday practice.The combination of the open design and the subjective, parent-reported outcomes does not control for the placebo effects, but will more closely reflect the benefits that would accrue in everyday practice with regard to analgesic effects.Contamination is possible given the over-the-counter availability of analgesic ear drops.

## Introduction

Although the current COVID-19 pandemic has a profound influence on the incidence of acute otitis media (AOM) in children,^1–3^ it will remain an important cause of primary care consultations.^4 5^ Ear pain is the predominant symptom and central to children’s and parents’ experience of the condition.^6 7^ High-quality studies have shown that most symptoms of AOM settle within a few days without antibiotics in otherwise healthy children living in high-income countries,^8^ but it may take 8 days for ear pain to fully resolve in 90% of the children.^9^ Globally, most AOM clinical practice guidelines therefore recommend oral analgesics in all, and antibiotics in selected, children.^10^ However, antibiotics are frequently prescribed in children with AOM,^4 5^ leading to side effects in at least 1 out of 10 children and emergence of antimicrobial resistance.^11 12^ Evidence of effectiveness of management options to relieve the most distressing symptom of AOM and reduce reliance on antibiotics is therefore urgently needed.^13^

Recently, we found that a general practitioner (GP)-targeted educational intervention to improve pain management in children with AOM resulted in an increase in oral analgesic use, in particular ibuprofen, but failed to reduce parent-reported ear pain and antibiotic use.^14^ Therefore, alternative interventions need further exploration. Analgesic ear drops, widely available, cheap and safe, may be well suited to fill this gap. When applied into the external auditory canal, these agents could relieve pain and distress by blocking nerve conduction of the tympanic membrane.^15^ So far, evidence on their use in children with AOM is limited.^15 16^ Our trial aims to produce this important evidence.

## Objective

The primary aim of this pragmatic randomised controlled trial is to investigate whether analgesic ear drops added to usual care (oral analgesics with/without antibiotics) provide superior ear pain relief over usual care alone in children presenting to primary care with AOM and ear pain.

## Methods and analysis

### Study design and setting

A pragmatic, two-arm, individually randomised, open, superiority trial with cost-effectiveness analysis in general practices in the Netherlands with a follow-up of 4 weeks will be performed. Potential trial participants will be recruited from primary care (approximately from 150 GPs) in the region of Utrecht, the Netherlands.

A mixed-methods process evaluation will be nested within the trial (see online supplemental material 1).^17–22^ This process evaluation will capture data to understand how participating in the trial has an impact on the consultation and behaviour and how AOM interventions (including analgesic ear drops, antibiotics and oral analgesics) are viewed by parents and GPs. The process evaluation consists of a survey with brief statements measuring attitudes of all parents based on the extended Common Sense Model^17^ and a three-item Consultation Satisfaction Questionnaire,^18^ and a qualitative part (semistructured interviews capturing parents and GPs’ views and experiences, respectively).

10.1136/bmjopen-2022-062071.supp1Supplementary data

### Participants

Children aged 1–6 years presenting to primary care with AOM^23^ and parent-reported ear pain in 24 hours prior to enrolment will be eligible for trial participation. Children with (suspected) tympanic membrane perforation or ventilation tube (as they carry a risk of inner ear damage causing hearing loss or tinnitus after application of lidocaine drops), ear wax obscuring visualisation of the tympanic membrane or those who are very unwell or require hospitalisation will be excluded. Detailed inclusion and exclusion criteria are listed in box 1.

Box 1Full list of inclusion and exclusion criteriaInclusion criteria:Age 1–6 years.Parent-reported ear pain in 24 hours prior to enrolment.General practitioner diagnosis of (unilateral or bilateral) acute otitis media.Exclusion criteria:Children:With (suspected) tympanic membrane perforation or ventilation tubes.With ear wax obscuring visualisation of the tympanic membrane.Who are systemically very unwell or require hospital admission (eg, child has signs and symptoms of serious illness and/or complications such as mastoiditis/meningitis).Who are at high risk of serious complications including children with known immunodeficiency other than partial IgA or IgG_2_ deficiencies, craniofacial malformation including cleft palate, Down syndrome and previous ear surgery (with the exception of ventilation tubes in the past).

### Study procedures and data collection

#### Recruitment and inclusion of participants

Figure 1 depicts a flow diagram of the study procedures. During regular primary care consultations, participating GPs will inform parents of potentially eligible children about the trial. Next, GPs will ask parents who are interested in participation for consent to provide their contact details to the study team at the University Medical Center (UMC) Utrecht. Members of the team will contact the parents by phone the same day to provide detailed information about the trial. If parents provisionally agree to participate and if the child fulfils the trial eligibility criteria, the study physician will visit the child at home. At this home visit, written informed consent for participation in the trial and the semistructured interview will be obtained (online supplemental material 2), baseline demographic and disease-specific data will be collected and a physical examination including otoscopy will be performed. Parents are also asked to complete generic and disease-specific quality of life questionnaires on behalf of their child. A full description of the nested process evaluation is given in online supplemental material 1.

10.1136/bmjopen-2022-062071.supp2Supplementary data

**Figure 1 F1:**
[figure not shown]
Flow diagram of study procedures. *Parents who gave consent for the semistructured interview will be recruited from both the intervention and control arm and will be purposively sampled after follow-up. AOM, acute otitis media; GP, general practitioner; OPTIMA, trial acronym.

#### Study group assignment

At the conclusion of the home visit, a trial randomisation website will be accessed for concealed study group assignment. An independent data manager generates a computer-generated randomisation sequence stratified for age (<2 years vs 2 years and above), AOM laterality (unilateral vs bilateral) and AOM baseline antibiotic prescribing (yes vs no). Children will be randomly allocated to either (1) lidocaine hydrochloride 5 mg/g (Otalgan) ear drops one to two drops up to six times daily for a maximum of 7 days^24^
^25^ with usual care (oral analgesics, with/without antibiotics); or (2) usual care. Analgesic ear drops will be provided by the study team. These drops should not be used in children with a tympanic membrane perforation or ventilation tube as they carry a risk of inner ear damage causing hearing loss or tinnitus. These children will therefore be excluded, as well as those with ear wax obscuring visualisation of the tympanic membrane. Parents of children allocated to the intervention group are expressly instructed to stop applying the drops if their child develops ear discharge.

The study team will notify the GP about the result of the randomisation. The local pharmacist will be notified in case the child is allocated to the analgesic ear drops, in order to check any known sensitivities/allergies and any interactions (with current or future drugs). Any treatment decisions other than the use of analgesic ear drops, that is, antibiotics and oral analgesics, will be left to the GP’s discretion in both groups. To those allocated to the intervention group, the study physician will not provide any treatment advice other than instructions about the use of analgesic ear drops. To those allocated to the control group, the study physician will not provide any treatment advice.

During follow-up, parents and GPs will be encouraged to manage AOM symptoms according to current clinical practice guidance on AOM in children issued by the Dutch College of General Practitioners. Lidocaine ear drops are currently not recommended in this guideline due to the lack of evidence.^23^

#### Follow-up data collection

Participants will be followed for 4 weeks. A telephone call will be scheduled at day 3, which will allow us to capture critical data on our primary outcome. Parents will keep a diary of AOM-related symptoms including ear pain scores and fever recordings, treatment adherence, prescribed and over-the-counter (OTC) medication use, AOM-related healthcare resource use, child care and travel costs, adverse events and complications of AOM for 4 weeks. At the end of follow-up, parents will complete a questionnaire on parental productivity losses and generic and disease-specific quality of life questionnaires. The diary and questionnaires can either be completed online or on paper forms (see the Data management section). The study team will contact the parents by phone to check if all data are collected. During this phone call, an appointment for the semistructured interview can be made with parents who are still willing to participate in the nested qualitative investigation.

#### Validated questionnaires used in the trial

Child’s ear pain intensity will be reported by parents in the symptom diary using a 0–10 Numerical Rating Scale, which has been validated for measuring pain in children with AOM.^26^Child’s symptoms of crying/distress, disturbed sleep, interference with normal activity, appetite, fever and hearing problems will be reported by parents in the symptom diary using a 0–6 Likert scale with higher scores indicating greater severity. This scale has been proven valid and was successfully used in our previous trials.^16 26^Generic quality of life of the child at baseline and 4 weeks will be assessed using the 47-item short-form of the Infant Toddler Quality of Life Questionnaire, which is developed for use in infants and toddlers aged 2 months–6 years and has shown to be a feasible instrument with adequate psychometric properties to discriminate between children with and without doctor-diagnosed respiratory disease.^27^Disease-specific quality of life of the child at baseline and 4 weeks will be assessed using the Otitis Media-6 Questionnaire.^28^Productivity losses (eg, parental absenteeism from work) because of AOM of their child will be assessed using the IMTA Productivity Cost Questionnaire (iPCQ) at 4 weeks.^29^

### Outcomes

#### Primary outcome

The parent-reported ear pain score over the first 3 days. To this end, parents will record their child’s ear pain scores during the first 3 consecutive days using a 0–10 validated Numerical Rating Scale.

#### Secondary outcomes

Proportion of children consuming antibiotics in the first 7 days.Oral analgesic use in the first 7 days.Overall symptom burden (crying/distress, disturbed sleep, interference with normal activity, appetite, fever and hearing problems) using a 0–6 Likert scale in the first 7 days.Number of days with ear pain during follow-up (4 weeks).Number of GP reconsultations with/without subsequent antibiotic prescribing during follow-up.Adverse events during follow-up.Complications of AOM during follow-up.Costs and cost-effectiveness during follow-up.Generic quality of life of the child at 4 weeks.Disease-specific quality of life of the child at 4 weeks.Parents’ and GPs’ views of treatment acceptability, usability and satisfaction.

### Sample size calculation

The main aim is to demonstrate that analgesic ear drops as added to usual care provide superior parent-reported ear pain relief over the first 3 days compared with usual care. In our recent trial, the mean parent-reported ear pain score (0–10 scale) over the first 3 days was 4.36 (SD 2.12) among those allocated to usual care.^14^ Patient and public involvement input from the UK suggested that a 1-point reduction (on a 0–10 scale) would be a clinically important difference.^16^ However, our parent panel felt that even a somewhat smaller difference would be clinically meaningful given the low-cost, low-risk nature of the intervention. To detect a pain reduction of 20% (reflecting a 0.87-point reduction in pain) compared with usual care with 90% power (beta 0.1) and at a 5% significance level (alpha 0.05), 126 children per group will be needed. To allow for 20% attrition, we aim to include 300 participants.

The estimated sample size will also provide substantial power to address the key secondary outcome of the proportion of children consuming antibiotics. Anticipating 47% of children consuming antibiotics in the usual care group as with our previous trial,^14^ 252 children will provide 89% power (beta 0.11; alpha 0.05) to detect a 20% difference in the proportion of children consuming antibiotics.

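### A target of 300 children does not allow for 20% attrition: it leaves 240 evaluable, not the 252 that the stated 90% power requires

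*Protocol article*

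**What the plan says.** All the relevant figures are in the section Sample size calculation of the protocol article.

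- Planning values from the previous trial: "the mean parent-reported ear pain score (0–10 scale) over the first 3 days was 4.36 (SD 2.12) among those allocated to usual care".
- Target effect: "To detect a pain reduction of 20% (reflecting a 0.87-point reduction in pain) compared with usual care".
- Error rates: "with 90% power (beta 0.1) and at a 5% significance level (alpha 0.05".
- Resulting requirement: "126 children per group will be needed", that is 252 in total. The abstract gives 1:1 allocation.
- Allowance for loss: "To allow for 20% attrition, we aim to include 300 participants".
- Key secondary outcome: "252 children will provide 89% power (beta 0.11; alpha 0.05) to detect a 20% difference in the proportion of children consuming antibiotics", with 47% anticipated under usual care.

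The article gives no inflation formula and no other attrition rule. Its second power statement treats 252 as the number available for analysis, which confirms how the first is to be read.

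**The concern.** If 252 evaluable children are needed and a fraction *d* of those randomised will be lost, the recruitment target is 252 / (1 − *d*). At *d* = 0.20 that is 315, not 300. The stated target is close to 252 × 1.2 = 302.4, which is what results from adding 20% to the requirement instead of dividing by the fraction retained.

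Recruitment target, tolerated attrition and power are the figures by which a reader later judges whether a trial was adequately sized, above all if the result is null. If losses fell between 16% and 20%, the protocol as written would say that the trial had met its design, although its own calculation says that it had not. Either the tolerated attrition or the power is overstated.

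**Working it through.** **Inputs** (Sample size calculation, except allocation, which is in the abstract): difference δ = 0.87; SD σ = 2.12; power 90%; alpha 0.05; 1:1 allocation; attrition 20%; target 300. Sidedness is not stated. Two-sided is assumed because it reproduces the plan's number; a one-sided test would need only 102 per group.

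**Step 1: reproduce the 126.** The effect 0.2 × 4.36 = 0.872 agrees with the stated 0.87. By the normal approximation,

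n per group = 2σ²(z₀.₉₇₅ + z₀.₉₀)² / δ² = 2 × 2.12² × (1.960 + 1.282)² / 0.87² ≈ 124.8, so 125.

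The two-sample t-test gives 125.75, so 126. The plan's requirement is confirmed, with t-test power of 90.1% at 126 per group.

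**Step 2: apply the attrition.**

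- Left after 20% loss from 300: 300 × 0.8 = 240, or 120 per group. Shortfall: 252 − 240 = 12.
- Needed to keep 252 after 20% loss: 252 / 0.8 = 315 (316 with equal arms of 158).
- Loss that 300 can absorb: 1 − 252/300 = 16%.
- Multiplying instead of dividing: 252 × 1.2 = 302.4.

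Rounding does not explain the gap, since 300 is 15 below 315.

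**Step 3: effect on the primary outcome** (two-sided t-test, δ = 0.87, σ = 2.12).

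| Evaluable | Per group | Loss from 300 | Power | Difference detectable with 90% power |
|---|---|---|---|---|
| 252 | 126 | 16% | 90.1% | 0.87 |
| 240 | 120 | 20% | 88.6% | 0.89 |

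The normal approximation gives 90.3% and 88.9% for the same two rows.

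**Step 4: effect on the antibiotic outcome.** The article states neither the scale of the 20% difference nor the test formula. Two assumptions reproduce its 89%: an absolute difference of 20 percentage points (47% against 27%) and a continuity-corrected comparison of two proportions. On that basis power is about 89% at 126 per group and about 87% at 120. Without the continuity correction the values are 91.3% and 89.9%. Read as a 20% relative reduction (47% against 37.6%), power at 126 per group would be only about 33%, so that is not the reading behind the stated figure.

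**The case against.** The strongest reply is that the power actually achieved may still reach 90%. The section Clinical effectiveness specifies a repeated-measures model adjusted for baseline ear pain, duration of pain and the stratification factors, whereas the calculation is an unadjusted comparison of one value per child. If baseline pain had a correlation ρ with the outcome, the residual SD would shrink by √(1 − ρ²). At 120 per group, ρ = 0.20 gives 89.8% power, 0.22 gives 90.1% and 0.30 gives 91.3%. Such a model can also use children with only some of the three daily scores. In addition, the 20% is not tied to a time point. Follow-up lasts 4 weeks, but the primary outcome ends at day 3 and is supported by a telephone call that day, so loss on that outcome may well be below 16%.

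This has force as to consequence, and it is why the point should not be read as a claim that the trial is underpowered. It does not rescue the statement. The article gives no correlation, uses no adjustment in its calculation and itself chose 20% as the loss to allow for; none of these arguments makes 300 × 0.8 equal 252.

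Two further points are fair. That the target came from multiplying by 1.2 is an inference, since no formula is shown and 302.4 is not exactly 300; the shortfall does not depend on it. And the antibiotic statement is not a second error: it is right for 252 children and merely inherits the shortfall.

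The size is also modest: 1.4 to 1.5 percentage points of power and 0.02 on a 0–10 scale. For the 1-point difference that the article cites as clinically important, 120 per group still give about 95% power.

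**Conclusion.** The concern holds. Within the article's own calculation, a target of 300, an attrition allowance of 20% and power of 90% for 0.87 points are not compatible. With 300 randomised, 90% power holds only up to 16% loss; at 20% loss it is 88.6%. The antibiotic power falls from 89% to about 87% under the same loss.

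The core finding (240 against 252) is plain arithmetic on stated figures. The power values rest on a two-sided unadjusted t-test with the stated SD and equal loss in both arms, and the antibiotic value on the two assumptions named in the working. This is a small misstatement of a figure that readers rely on, worth correcting, and not evidence of a materially underpowered trial.

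**What to change.** Keep the target of 300 and correct the sentence in one of two ways:

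- state that 300 children allow for 16% attrition around the 252 required; or
- keep 20% attrition and state that it leaves 240 evaluable children, with about 88.6% power for a 0.87-point difference.

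Quote the antibiotic power at the same evaluable number: 89% if the 16% wording is used, about 87% if the 20% wording is used. Say there that the difference is 20 percentage points and which formula was applied.

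The cost is a sentence or two of text and slightly less favourable stated figures. No additional children are needed, and design, conduct and analysis do not change. Raising the target to 315 (316 with equal arms) would also remove the contradiction, but the size of the effect does not call for it.

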### Data management

During study conduct, we will comply with the European Union General Data Protection Regulation and the Dutch Act on Implementation of the General Data Protection Regulation. The data management department of the Julius Center, UMC Utrecht will be responsible for handling and storage of the trial data using a secured and coded online database (Research Online 2.0 (RO 2.0)). Data will be either entered directly into RO 2.0 or collected on paper forms first. For data entered directly into RO 2.0, processes to promote data quality are added. Coded trial data will be securely stored for 25 years in the main study folder on a central drive of the Julius Center.

